
### Statistics

#### Sample size

Below are given details on the sample size estimation for primary clinical outcomes. However, aside from statistical power, a sufficiently large sample is necessary to obtain representative results for the general population and to allow sustainable statements on the effectiveness and efficiency of the intervention for secondary clinical as well as economic outcomes. We therefore plan to include all eligible patients willing to participate in the study and finally assume a number of n = 700 in each group. This number takes into consideration the degree of capacity utilization of hip and knee training courses as well as the number of subjects non eligible due to inclusion- and exclusion criteria as well as subjects refusing consent to participate in the study (Fig. 1).

The empirical basis of the sample size estimation for primary outcomes was retrieved from the paper by Krauss et al. [17]. In this randomized controlled trial (RCT), intra-individual differences of WOMAC subscale pain and WOMAC subscale physical function identically showed an effect size of about 0.5 between the intervention and the control group (pain, intervention: −8.5 ± 13.9, control: −1.3 ± 15.3, physical function, intervention: −8.4 ± 13.4, control: −2.1 ± 12.9).

Based on the previous results of the RCT and the so-called efficacy-effectiveness gap between RCTs and studies under real life conditions [32] we finally assume an effect size of ES = 0.3.

Due to the fact that we want to test the two endpoints (pain and physical function) simultaneously and without hierarchical order, we choose a level of significance of 0.025 (two-sided, Bonferroni correction) and a power of 0.90. This leads to a sample size of 278 subjects per group in the parallel group design without cluster effects (nquery release 7.0). The drop-out rate in the intervention group of the above mentioned RCT was 8 % [17]. As this value is quite low, we assume a somewhat higher number of non-finishers and estimate the rate to be 20 %. Thus 350 subjects should be allocated to each treatment arm.

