The finally defined controls and cases will be included into a linear model with the propensity score as covariate. Additionally, we will use models for longitudinal data using each measurement point (instead of only t0 and t3 for the primary analysis). The level of significance will be 0.025 for primary endpoints. Secondary endpoints will be analyzed analogously without claiming confirmatory interpretation of *p*-values.

Descriptive analysis will include absolute and percentage frequencies for categorical variables, means, medians, standard deviations, quartiles and ranges for quantitative variables and medians, quartiles and ranges for ordinal variables. For the main results, two-sided 95 % confidence limits will be given additionally to significance tests. For percentages exact confidence interval for proportions based on the binomial distribution will be given.

Exploratory, prognostic factors will be analyzed using multiple regression models (linear regression) to identify potential responders to the training.

Correlation analyses will use Pearson product moment correlation coefficient (normally distributed variables) and Spearman correlation (non-normally distributed variables).

The primary analysis will be done on the full set of patients recruited in consideration of the exclusion criteria “limited pain and impairment in physical function” (WOMAC Index subscales pain and physical function with values below 15) except for patients refusing consent during the study and obviously wrongly diagnosed patients. A secondary analysis will be done using the full set of eligible and included patients irrespective of their limitations in pain and physical function at baseline (t0). This secondary analysis will only claim confirmatory interpretation of p-values if the primary analysis is able to detect group differences in a statistical manner. Otherwise the secondary analysis will be done in an explorative manner.

Missing values will be imputed using multiple imputation approaches, complete case and last observation forward analysis will be performed as a sensitivity analysis. No interim analysis, except for administrative purposes will be performed. All statistical analysis will be done using the software SPSS and R in the newest release.

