## Discussion

Despite the strong evidence for the short-term effects of physical exercises on symptoms in knee and hip OA [8, 15, 16], many open questions remain with respect to (I) the incorporation of interventions into patient care in a regular health care setting, (II) long-term effects of the intervention as well as its impact on disease progression, (III) dose–response-relationship according to FITT principles (frequency, intensity, type and time of training) and (IV) knowledge on variables that act as confounders for treatment response. Open questions are also related to (V) the economic efficiency of exercise interventions in the treatment of hip and knee OA and to (VI) safety aspects of the intervention [8, 11, 15].

This study proceeds in a real health care setting and has the potential to answer questions in the aforementioned research areas.

(I) This study allows us to determine whether the efficacy of an exercise intervention proofed in a randomized controlled trial can be transferred into effectiveness into a real life situation with less standardized and controlled conditions. The intervention described in this study protocol has been derived from a previously tested exercise intervention in patients with hip OA [17, 20]. Yet some adaptations to the intervention had to be made to give consideration to the needs and organizational framework of the health care provider: the formerly 12-week intervention with one supervised session/week and two additional home-exercise sessions/week was reduced to 8 supervised sessions. Patients are instructed to perform the accompanying home-exercise sessions for at least 11 weeks according to the exercise manual every participant receives [21]. Aside from this change that is related to the frequency and duration of the exercise intervention, the population under consideration has been extended: the RCT was conducted on subjects with hip OA only. As prevalence for knee OA in comparison to hip OA is even higher, the program will be offered to patients with hip and/or knee OA. Subjects with knee OA will therefore substitute some of the hip-exercises with knee-specific exercises. On this note, subjects with knee OA receive an amendment for the exercise manual with knee-specific exercises. Results of this study are therefore very valuable as they allow us to verify whether an “evidence-based exercise intervention” can successfully be implemented into everyday routine or not.

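### At t6, t12 and t24 neither named sensitivity analysis tests loss of benefit in intervention patients lost after t3, and LOCF holds their end-of-training score for up to 21 months

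*Protocol article*

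**What the plan says.** The section Matching procedures and statistical analysis of clinical endpoints names the methods: "Missing values will be imputed using multiple imputation approaches, complete case and last observation forward analysis will be performed as a sensitivity analysis". It gives no imputation model and names no analysis that varies the assumption about missing patients.

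The same section makes the primary analysis a comparison using t0 and t3 only. It adds longitudinal models over all visits and covers the later visits with: "Secondary endpoints will be analyzed analogously without claiming confirmatory interpretation of" p-values.

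Study purpose lists mid-term and long-term pain and function as secondary aims II and III. The Discussion asks whether efficacy shown in a randomised trial "can be transferred into effectiveness into a real life situation with less standardized and controlled conditions".

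On attrition, Sample size says of the earlier trial: "The drop-out rate in the intervention group of the above mentioned RCT was 8" %. For this study, "we assume a somewhat higher number of non-finishers and estimate the rate to be 20" %. That rate is used only to enlarge the sample.

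**The concern.** Aims II and III ask whether a benefit present at the end of training is still there months later. The sensitivity analyses should therefore challenge the assumption that patients who disappear kept their benefit. For patients lost after t3 the two named analyses do not. Complete case repeats the assumption behind standard multiple imputation, and LOCF builds persistence into the data.

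The protocol itself gives a reason to expect the contrast to shrink. According to the Discussion, controls may join the same training during follow-up, and separation of the groups is assured only for the first three months. LOCF keeps the contrast from before that point. The 24-month results also matter in practice, because the Discussion says that positive ones may prompt a 5-year extension.

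**Working it through.** **Inputs.** From Sample size: planning effect 0.30 ("we finally assume an effect size of ES = 0.3"), alpha and power ("we choose a level of significance of 0.025 (two-sided, Bonferroni correction) and a power of 0.90"), 20 % non-finishers, 700 per arm, cluster inflation factor 2 in the intervention arm, and the earlier trial's changes ("pain, intervention: −8.5 ± 13.9, control: −1.3 ± 15.3"). My assumptions, since the protocol gives no loss rate after t3 and no expected t24 effect: 20-30 % lost after t3 in both arms, and an effect of 0.30 at t3 in them as in the others.

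**1. The plan's own figures.** n = 2 × (2.2414 + 1.2816)² / 0.30² = 276 per group by normal approximation. The t-test solution is 277.06, hence the stated 278. Then 278 / 0.8 = 347.5, that is 348, against 350 stated. The design effect is 1 + 3 × 0.33 = 1.99. The sample size reproduces and is not affected by this point.

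**2. What each analysis returns at t24.** Let p be the share lost after t3, e the t24 effect in those still answering and d the t24 effect in those lost.

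- Truth: (1 − p)e + pd
- Complete case and standard multiple imputation: about e
- LOCF: (1 − p)e + 0.30p
- Control-based imputation: (1 − p)e

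*Benefit wanes equally in everyone (d = e):*

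| True t24 effect | LOCF, p = 0.20 | LOCF, p = 0.30 |
|---|---|---|
| 0 | 0.06 | 0.09 |
| 0.10 | 0.14 | 0.16 |
| 0.15 | 0.18 | 0.195 |
| 0.30 (no waning) | 0.30 | 0.30 |

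*Benefit lasts in those answering and is gone in those lost (e = 0.30, d = 0):* the truth is 0.8 × 0.30 = 0.24, or 0.7 × 0.30 = 0.21. Multiple imputation and complete case give about 0.30. LOCF gives 0.8 × 0.30 + 0.2 × 0.30 = 0.30, and likewise 0.30 at p = 0.30. All three planned analyses agree and none shows the loss. Control-based imputation gives 0.24 or 0.21.

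Whenever e is at most 0.30, LOCF is at least as favourable as e. For losses after t3 it therefore cannot act as the cautious check.

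**3. Losses before t3.** LOCF now carries baseline and returns (1 − p)e. With a true effect of 0.15 and p = 0.20 it gives 0.12, an understatement. With 10 % lost before and 10 % after t3 it gives 0.8 × 0.15 + 0.1 × 0.30 + 0.1 × 0 = 0.15, correct only by cancellation.

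**4. Nominal significance of the LOCF result when the true t24 effect is 0** (700 per arm, unit SD, two-sided 0.05, favouring training):

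- With factor 2 in the intervention arm, SE = √(1/700 + 2/700) = 0.0655. Shifts of 0.06 and 0.09 give 15 % and 28 %.
- Without clustering, SE = √(2/700) = 0.0535, giving 20 % and 39 %.

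**5. LOCF at t3.** The last earlier value is t0, so a missing patient has change 0. For pain with 20 % missing in both arms, LOCF gives 0.8 × (−8.5 + 1.3) = −5.76. A control-based rule gives 0.8 × (−8.5) + 0.2 × (−1.3) + 1.3 = −5.76. With 20 % missing in the intervention arm only, LOCF gives 0.8 × (−8.5) + 1.3 = −5.50. All are smaller than the complete-data −7.2.

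**The case against.** **LOCF is only a sensitivity analysis of non-confirmatory endpoints.** This is true and limits the weight of the point. A reader might also infer that LOCF would manufacture a 24-month effect that confirms the main result. The documents do not support that. Multiple imputation is the main method, and if the effect has vanished in everyone it also gives about 0, so an LOCF result of 0.06-0.09 would disagree with it. What stands is the other case in step 2, where the planned analyses agree because none looks at the patients lost.

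**The direction of bias is not fixed.** Also true: it needs waning and loss after t3. But a check whose bias depends on when patients leave is hard to interpret either way.

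**A reader might infer that the primary t3 effect is overstated because 20 % non-finishers are credited with the finishers' benefit.** The arithmetic is easy: 0.8 × 0.30 = 0.24 against 0.30, and a simulation of multiple imputation ignoring adherence returned 0.297 for a truth of 0.24. The documents do not carry it, for four reasons.

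- Questionnaires come by post and the primary set keeps all recruited patients above the WOMAC floor, apart from consent refusals and wrong diagnoses. A patient who stops training can still have an observed t3 value.
- The imputation model is not stated, which a protocol may leave to the analysis plan. Adherence could enter it. With half of the non-finishers returning the t3 form and adherence in the model, the simulation gave 0.243. One caveat remains: adherence is collected on the t3 questionnaire, so it is absent for those who do not return it.
- The 0.30 was obtained by lowering about 0.5 for real-life conditions. The protocol does not present it as an effect in finishers.
- LOCF at t3 is already conservative (step 5).

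**The additional longitudinal models might help.** They use all visits, but the protocol describes nothing in them that varies the assumption about lost patients.

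**Conclusion.** The point holds for t6, t12 and t24. For intervention patients lost after t3, complete case shares the assumption of standard multiple imputation, and LOCF assumes that the end-of-training value persists. No named analysis tests loss of benefit in them, although persistence is what aims II and III ask about.

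With 20-30 % lost after t3, 0.30 at t3 and no true t24 effect, LOCF shows 0.06-0.09 and is nominally significant in favour of training in 15-39 % of trials, depending on clustering. Without waning there is no such overstatement, and with losses before t3 LOCF can understate. The loss rates and the t24 effects are assumptions.

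The confirmatory t3 analysis is not shown to be biased, and it already has a conservative check. This is a cheap improvement, not a flaw in the primary analysis.

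**What to change.** Change the missing-data sentence so that, at t6, t12 and t24, LOCF is replaced by one of these as the sensitivity analysis to the planned multiple imputation:

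- **Control-based (jump-to-reference) imputation.** Missing WOMAC values of intervention patients are drawn from the matched-control distribution given baseline, and missing controls are imputed under missing at random.
- **Delta-adjusted imputation.** Imputed intervention values are worsened by a range of amounts, for instance 0 to 0.30 SD. With 20 % missing this moves the estimate by up to 0.2 × 0.30 = 0.06.

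Because controls may take up the training during follow-up, the control reference is not purely untreated. This is a reason to consider the delta version or to report both.

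Report the same analysis at t3 beside the planned ones; baseline carried forward can stay there. Do not make it a condition of the t3 claim. That would change the confirmatory rule and cost power: with 560 analysed per arm, a factor of 1.99 in both arms and alpha 0.025, power is about 91 % at 0.30 and about 73 % at 0.24.

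The cost is one changed sentence and some programming in R, with no new data or patients. The downside is a somewhat less favourable sensitivity estimate, for example 0.24 where the planned analyses show 0.30 with 20 % missing.

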#### Economic evaluation

Cost-efficiency of the intervention will be quantified on the expanded perspective of the payer. If a dominant strategy doesn’t exist (i.e.: lower costs and higher health related effects in the intervention group), the costs will be related to the effects. The costs (including the supplementary costs of the pilot offer for participants) will be related to the differences between the groups (Double-Difference Method, two years pre and two years post intervention) in Quality Adjusted Life Years (QALYs, equation 1) and health related effects (WOMAC Index: equation 2). The costs of the intervention will further be related to the differences in costs (Double-Difference Method of the health care costs (unspecific health care costs (overall costs), specific health care costs and the costs for days of disability (human capital approach): equation 3). The time to surgery will be estimated using the Kaplan-Meier method. For the economic evaluation all participants have to be members of the insurance the period from 24 months before baseline (tm24) up to 24 month after baseline (t24).

Equation 1: Cost-Utility Analysis (CUA) = Incremental Cost Utility Ratio (ICUR)$$ ICUR\kern0.49em =\kern0.49em \frac{\varDelta\ \mathrm{Cost}}{\varDelta\ \mathrm{QALYs}} $$

Equation 2: Cost-Effectiveness Analysis (CEA) = Incremental Cost-Effectiveness Ratio$$ ICER\kern0.49em =\kern0.49em \frac{\varDelta\ \mathrm{Cost}}{\varDelta\ \mathrm{Effect}} $$

Equation 3: Cost-Benefit Analysis (CBA) = Incremental Cost-Benefit-Ratio$$ ICBR\kern0.49em =\kern0.49em \frac{\varDelta\ \mathrm{Cost}}{\varDelta\ \mathrm{Benefit}} $$

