## Methods/design

### Design (Fig. 1)

**Fig. 1 Fig1:**
[figure not shown]
Study flow chart

This is a multi-center non-randomized controlled trial of an 11-week hip and knee training (HKT) with a 24 months follow-up period in the context of health services research. The exercise intervention comprises 8 supervised group sessions (1× / week for 8 weeks) and a home exercise program (2× / week for 11 weeks). All participants are insurance holders of a large statutory health insurance company covering approx. 40 % of the total population of the state Baden-Wuerttemberg. Participants of the intervention group (IG) will be compared to “statistical twins” (matched pairs) to investigate the effects of an exercise intervention on clinical and economic outcomes. Measurements will be taken at baseline (t0), 3 months (t3), 6 months (t6), 12 months (t12) and 24 months (t24). Economic data will further be evaluated retrospectively for two years prior to baseline.Recruitment of the intervention group (IG)IG is recruited out of eligible participants of a countrywide health care offer of the above mentioned insurance company. Prerequisites for exercise participation are (1) membership in the insurance company, (2) referral from an orthopaedic surgeon or general practitioner because of complaints at the hip and/or knee. To be included into the accompanying study, exercise participants further have to confirm a self-reported lifetime prevalence of hip and/or knee OA. They have to affirm the following two questions according to the German Federal State health reporting system criteria [2]:1. “Have you ever visited a doctor because of complaints in the hip and/or knee joint?”2. “If yes, did a medical doctor ever ascertain OA or a degenerative disorder at your knee and/or hip joint?”Further inclusion- and exclusion criteria for study participation are listed in Table 1.

**Table 1 Tab1:** Inclusion and exclusion criteria for study participation (t0 = baseline)

Inclusion criteria (all criteria relevant for study eligibility)
• Insurance holder of the insurance company offering the exercise program since two or more years prior t0
• Referral from an orthopaedic surgeon or general practitioner
• Self-reported lifetime prevalence of hip and/or knee OA that was previously diagnosed by a medical practitioner • Physical and mental ability to participate in the interventional program and to answer self-administered questionnaires at t0

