### Collection points (Fig. 5)

**Fig. 5 Fig5:**
[figure not shown]
Collection points and outcome measures. Figure legend: t = collection point, m = minus. 0, 3, 6, 12, 24 = month of collection point related to baseline (t0)

Participants will be assessed at baseline (t0) and after (t3) the 11-week intervention period. Three follow-ups are conducted by mail 3 (t6), 6 (t12) and 21 (t24) months after the end of the intervention period. Economic evaluation will further compare data 6 (tm6), 12 (tm12), 18 (tm18) and 24 (tm24) months retrospectively (m = minus) prior to t0.

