### Outcome measures (Table 4, Fig. 5)

**Table 4 Tab4:** Outcome measures

Characteristics & confounders	Description and instrument	Data source	Sample	Collection points
Patient’s characteristics	Date of birth, gender, ethnicity, BMI (height, weight), site (s) of OA diagnosis, date of first OA diagnosis, labour situation (working, retired, unemployed, in rehabilitation status)	SAQ, IDB	IG, CO	t0, t3, t6, t12, t24
Primary outcome measure	Clinical Outcomes			
Pain	WOMAC Index 3.1 German (11-box NRS): subscale pain	SAQ	IG, CO	t0, t3
Function	WOMAC Index 3.1 German (11-box NRS): subscale physical functioning	SAQ	IG, CO	t0, t3
Secondary outcome measures	Clinical Outcomes		IG, CO	
Stiffness, disease specific impairment	WOMAC Index 3.1 German (11-box NRS): subscale stiffness, overall score	SAQ	IG, CO	t0, t3, t6, t12, t24
Pain, physical function	WOMAC Index 3.1 German (11-box NRS): subscale pain, subscale physical function	SAQ	IG, CO	t6, t12, t24
Health related quality of life	VR-12 incl. VR-6D utility index (4-week-time-slot)	SAQ	IG, CO	t0, t3, t6, t12, t24
General Self-Efficacy	General self-efficacy scale (GSE)	SAQ	IG, CO	t0, t3, t6, t12, t24
Response to exercise	Omeract-OARSI Set of Responder Criteria: composite score with minimum absolute and relative change levels for pain or pain & function	SAQ	IG, CO	t0, t3, t6, t12, t24
Physical activity status	Habitual physical and sports activity status	SAQ	IG, CO	t0, t3, t6, t12, t24
Time to surgery	Endpoint “elective joint replacement”	IDB	IG, CO	t0, t3, t6, t12, t24
	Patient satisfaction			
	Modified version of the ZUF-8 Questionnaire to assess patient satisfaction	SAQ	IG	t3
	Economic data			
Unspecific and specific (OA-related) health care costs	Out-patient costs, hospital costs, costs related to drugs, adjuvants and physical modalities, rehabilitation costs, sick-pay	IDB	IG, CO	tm24, tm18, tm12, tm6 t0, t3, t6, t12, t24
Unspecific/specific (OA related) periods of disability	Days of disability (overall and related to OA)	IDB	IG, CO	tm24, tm18, tm12, tm6 t0, t3, t6, t12, t24
Intervention related costs	Costs for human and physical resources/session	IDB	IG	t3, t6, t12, t24
	Adherence to exercise			
Training adherence	Summarized number of attended training sessions according to training log	SAQ	IG	t3
	Safety evaluation			
Adverse events and side-effects	Summarized number and details of adverse events and side-effects according to training log	SAQ	IG	t3

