Patient satisfaction (IG only, t3) will be quantified by participants of the IG with a four point Likert scale using a modified and shortened version of the ZUF-8 [30, 31]. Modifications were made in order to adapt the eight item instrument to the outpatient setting.Patient characteristicsBody Mass Index (BMI), site (s) of OA joint diagnosis, artificial joint replacement (hip or knee and time of event).Safety evaluation (IG only, t3)Description of adverse events within the previous 11-week intervention period including frequency, intensity and duration of exercise related pain and possible reasons. Participants get a training log for home-based exercises where they are asked to report adherence as well as exercise related adverse events. In this way summarized data can be provided by the participants at the end of the intervention period by reviewing the training logs. Aside from this study-related safety report, patients are urged to contact their personal trainers or physicians in case of adverse events and side-effects.Adherence to exercise (IG only, t3)Number of attended training sessions (group and home-based exercises). In case of omitted sessions: Reasons for non-compliance.Socio-demographic data (insurance data base)The following socio-demographic data will be readout of the data base: date of birth, gender and labor situation (working, retired, unemployed, in rehabilitation status), complexity of work (from 1 = low to 4 = high), level of education (1 = no graduation to 4 = High School), highest level of educational attainment (from 1 = no qualification to 6 = doctoral degree), contractual form (permanent/fixed term contract, full time/part time).Economic data (insurance data base)Patient-specific economic data comprise (1) unspecific and (2) specific osteoarthritis related health care costs for the diagnosis of hip and/or knee OA, (3) Specific and unspecific days of disability and (4) intervention related costs for the exercise program:(1) Unspecific health care costs (overall costs): Sick-pay, hospital costs, out-patient costs, rehabilitation costs and costs related to drugs, physical modalities and adjuvants.(2) Specific diagnosis (hip and knee OA) related health care costs: Sick-pay, hospital costs, out-patient costs, rehabilitation costs and costs related to disease related drugs, physical modalities and adjuvants.(3) Specific (hip and knee OA related) and unspecific days of disability.(4) Intervention related costs include human and physical resources that are required for the institutional exercise sessions. Intervention related costs will be added to the above mentioned diagnosis related costs for all participants of the intervention groups according to the number of their scheduled training session (8 units).

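### The two-year pre/post double difference is applied to QALYs and WOMAC, which have no data before t0; separately, the text leaves open whether intervention cost enters both sides of Equation 3

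*Protocol article*

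**What the plan says.** All references are to the protocol article.

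**Contrast for the effects.** The Economic evaluation section relates costs to group differences, and describes those differences as "Double-Difference Method, two years pre and two years post intervention) in Quality Adjusted Life Years (QALYs, equation 1) and health related effects" (WOMAC, Equation 2).

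**When the effects are measured.** QALYs come from the "VR-12 incl. VR-6D utility index (4-week-time-slot") row of Table 4, a self-administered questionnaire at t0, t3, t6, t12 and t24. WOMAC pain and function are listed at t0 and t3 as primary outcomes and at t6, t12 and t24 as secondary outcomes. The row "WOMAC Index 3.1 German (11-box NRS): subscale stiffness, overall score" covers t0 to t24. The Collection points section confirms the start: "Participants will be assessed at baseline (t0) and after (t3) the 11-week intervention period".

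**What exists before t0.** The Design section says "Economic data will further be evaluated retrospectively for two years prior to baseline", and Collection points says "Economic evaluation will further compare data 6 (tm6), 12 (tm12), 18 (tm18) and 24 (tm24) months retrospectively (m = minus) prior to t0". In Table 4 only the cost and disability-day rows carry tm24, tm18, tm12 and tm6.

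**Equation 3.** "The costs of the intervention will further be related to the differences in costs": the differences meant are double differences in overall costs, OA-specific costs and disability-day costs valued by human capital. Intervention cost is not in that list. The economic-data part of the outcome section, however, says "Intervention related costs will be added to the above mentioned diagnosis related costs for all participants of the intervention groups", on the basis of eight scheduled sessions.

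**The concern.** A double difference needs a pre-period quantity and a post-period quantity for each group. For QALYs and WOMAC the schedule supplies no pre-period quantity, so the specified denominators of Equations 1 and 2 do not exist. An analyst would have to choose a substitute that the text does not name, and different substitutes estimate different things.

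In Equation 3, C is the numerator. If C has also been booked into the OA-specific costs of intervention participants, it reduces the measured saving in the denominator. The ratio would then no longer show what the programme saves per euro spent on it.

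The Discussion describes cost-utility as of special interest and gives power for the economic evaluation as a reason for including every eligible, willing patient. The definitions should therefore be settled before the economic data are analysed.

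**Working it through.** The article states no figure for any of the three ratios, so there is none to reproduce. The check compares the prescribed contrast with the measurement schedule, then works through the algebra of Equation 3.

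**1. Data available on each side of t0 (Table 4)**

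| Quantity | Points before t0 | Points from t0 |
|---|---|---|
| Costs, disability days | 4 (tm24, tm18, tm12, tm6) | 5 |
| VR-6D | 0 | 5 (t0, t3, t6, t12, t24) |
| WOMAC | 0 | 5 (t0, t3, t6, t12, t24) |

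The prescribed contrast is (post − pre) in the intervention group minus (post − pre) in the control group, each period lasting 24 months. It can be computed for costs and disability days. For VR-6D and WOMAC the pre term is empty. The VR-6D recall window is four weeks, so even the t0 value describes at most the last four weeks before baseline, not two years.

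**2. What can be computed for the effects**

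A QALY total over t0 to t24 is available as the area under the VR-6D curve. With visits at 0, 3, 6, 12 and 24 months, the trapezoid weights in years are half the adjacent intervals divided by 12:

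- t0: 3/24 = 0.125
- t3: (3 + 3)/24 = 0.25
- t6: (3 + 6)/24 = 0.375
- t12: (6 + 12)/24 = 0.75
- t24: 12/24 = 0.5

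They sum to 2.0 years. The t0 value can serve as a covariate, and the same holds for WOMAC at follow-up. No new data are needed.

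**3. Equation 3**

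Let C be the intervention cost per participant. Let S be the gross double-difference saving in OA-specific costs, before any intervention cost is booked.

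- C kept out of the health care costs: ratio = C/S.
- C added to the post-period OA-specific costs of intervention participants: the measured saving is S − C, and the ratio = C/(S − C).

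The article gives no euro amounts, so S/C is an assumption shown over a range.

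| Assumed S/C | C/S | C/(S − C) |
|---|---|---|
| 0.5 | 2.00 | −2.00 |
| 1 | 1.00 | undefined |
| 1.5 | 0.67 | 2.00 |
| 2 | 0.50 | 1.00 |
| 3 | 0.33 | 0.50 |
| 5 | 0.20 | 0.25 |
| 10 | 0.10 | 0.11 |

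C/S equals 1 when the programme just pays for itself. C/(S − C) equals 1 only when the saving is twice the cost. It has no value at break-even and is negative below it.

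**4. Reach of the Equation 3 problem**

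The outcome section adds C to OA-specific costs only, so the overall-cost and disability-cost components are untouched. For Equations 1 and 2, the Economic evaluation section says that costs include those of the offer. If OA-specific costs already containing C are used there, the text does not exclude adding C again. Sick-pay is part of both cost totals, and disability days are also valued by human capital. The same absence would be counted twice only if these components were summed.

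**The case against.** On the effects, the other side can say that one phrase has been stretched over two data types. Measured t0 values exist for both instruments, the matching section already refers to a t0 QALY value from VR-6D, and a change-from-t0 contrast is available from the planned questionnaires. That stands as a reason to call the defect repairable. It does not rescue the text: a change from one baseline visit is not a two-year pre-period. The article specifies the contrast itself, so this is not detail merely left to a fuller plan.

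On Equation 3, the objection is stronger. The Economic evaluation section does not list intervention cost among the denominator components. Table 4 gives it a separate row, and the outcome section numbers it as a separate item. A reader might infer that the plan explicitly puts C on both sides. The documents do not support that: the double count arises only when the booking rule in the outcome section is carried into Equation 3, and only for OA-specific costs. A reader might likewise infer that absences are certainly counted twice, but the article never says that the cost components are summed.

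The area-under-the-curve form and regression adjustment are reasonable choices rather than the only possible repair. Some detail of that kind could sit in an analysis plan not shown here.

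**Conclusion.** The first part holds without assumptions: by the article's own schedule, the two-year pre/post double difference cannot be formed for QALYs or WOMAC.

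The second part holds conditionally. If the OA-specific costs used in Equation 3 contain intervention cost, as the outcome section's booking rule implies, that component's ratio is C/(S − C) rather than C/S. The effect depends entirely on the unknown S/C. It is small at S = 10C, a doubling at S = 2C, and a loss of meaning at or below S = C. This is an ambiguity to close, not a stated rule.

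A reader might conclude that the economic ratios as a whole are invalid. That goes too far: the ratio forms are standard, the cost double difference is feasible with tm24 to t24 data, and usable effect contrasts can be built from t0 onward. The outcomes are secondary and carry no confirmatory claim. The primary WOMAC analysis at t3 is not affected. The correction should be made, but it does not threaten the trial's main conclusion.

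**What to change.** Rewrite the Economic evaluation paragraph, and the matching sentence in the outcome section, to say:

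- The two-year pre/post double difference applies to costs and disability days only.
- The QALY difference is the between-group difference in area under VR-6D from t0 to t24, adjusted for t0 VR-6D.
- The effect difference for Equation 2 is WOMAC at a named follow-up visit, adjusted for t0 WOMAC.
- Intervention cost is kept as a separate line. It is included exactly once in the cost difference for Equations 1 and 2, and the health care costs forming the Equation 3 benefit exclude it.
- If cost components are summed, each absence day is valued once, either as sick-pay or by human capital.

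The cost is a few sentences of text, settled before the economic data are analysed. No new data, visits or participants are needed.
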